### Ethical considerations

All participating study centres and parents received detailed written information on research goals, study procedures, data analyses and data reporting prior to participation. Written consent is obtained from all parents and children before entering the study and saved by the research team at the Catholic University of Applied Sciences North Rhine-Westphalia. Participants assigned to control condition I are asked to participate in the evidence-based original “Trampoline”-programme. Participants from control condition II have volunteered to participate in this group or are assigned to it for practical reasons with their informed written consent. They also receive TAU. All participating children and parents are encouraged to call the research group in case of arising questions or problems. In case of unexpected severe adverse events (SAE) the participating study centres are obliged to document and report these to the research team. It will then be decided on how to proceed (e.g. remove participants from intervention, initiate medical help).

All data processing will be conducted according to the current Data Protection Act. The research team at the Catholic University of Applied Sciences North Rhine-Westphalia has access to the final data set.

The ethics committee of the Catholic University of Applied Sciences North Rhine-Westphalia in Cologne, Germany, has approved all procedures.

A neutral data management security board (DSMB) and an external monitoring agency will supervise the adherence of the study to Good Clinical Practice (GCP) standards.

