### Sample

Participants are CSP recruited by the participating study centres with the help of information materials provided by the research team at Catholic University of Applied Sciences North Rhine-Westphalia. Study centres inform participants and parents about the content and goal of the programme and study and screen participating CSP for eligibility. Inclusion criteria are:children aged between 8 and 12 years (exceptions made for 7- and 13-year olds; see above) at T0,children currently situated at an inpatient or outpatient psychiatric treatment or psychiatric day care or inpatient youth welfare service,children exposed to parental substance use within last year (“parent” may also be a caregiver),children either living with the substance-affected parent or having regular contact with him or her (at least once a month),positive screening of parent on Alcohol Use Disorder Identification Test (AUDIT) [40] and/or Drug Use Disorder Identification Test (DUDIT) [41, 42] (and/or optional: positive screening of child on Children of Alcoholics Screening Test (CAST)) [43, 44],sufficient mastery of the German language by both children and parents to participate in assessments andinformed written consent from both parents and children.

Children are excluded from the study ifthey are diagnosed with or suspected of foetal alcohol spectrum disorder and/or cognitive impairment and/or severe conduct disorder or ifthey have received any kind of addiction-specific treatment relevant for the study goals six months prior to the study or ifthey have insufficient German language skills.

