Quality of relationship between parents and child	Own development: questions on a thermometer-scale in regard to closeness vs. distance and harmony vs. conflict
Parental use of substance-related help	Own development
Mental health problems	SCL-K-9 (Symptom Checklist, short version)
Parental alcohol problems	AUDIT (Alcohol Use Disorders IdentificationTest)
Parental drug problems	DUDIT (Drug Use Disorders Identification Test)
Experience with mindfulness-based interventions	Own development
Mindful attention awareness	MAAS (Mindful Attention Awareness Scale)

In each condition, all participating children will receive a 10,00€ gift card as compensation for their participation at all points of measurement.

Besides analyzing data on the effectiveness of the “Trampoline-Mind” and “Trampoline”-programme, process evaluation data is collected as well. For this, trainers from the participating centres are asked to complete short questionnaires on adherence, group interaction and challenges encountered after each child and parent session. Moreover, trainers are asked to complete questionnaires on relevant characteristics such as structural data on their institution or professional background. In addition, process evaluation data from children and parents are gathered after each session. These data will be useful for analyzing e.g. the quality of manual adherence. Moreover, the data can help identifying potential moderating factors such as trainer qualification or group dynamics.

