### Limitations

Due to the volatile nature of substance-involved families and high fluctuations the clinical or youth welfare setting, it might become challenging to motivate CSP to run through the programme entirely and/or reach them to participate in follow-up measurements. Also, many parents with SUD will not let their children participate in the programme because of denial or feelings of shame and guilt, thereby creating a selection effect in the sample. Moreover, CSP may be reluctant to participate because of the fear of stigmatisation by other children residing in their study centre. All reasons for rejections and dropouts are to be documented and will be analysed carefully.

Because of these recruitment issues, this study – which had been originally planned as a randomised-controlled study – has been transformed into a cRCT. It became clear early on that cooperating study centres will not be able to perform two parallel groups, delivering both the “Trampoline-Mind” and the original “Trampoline”-programme simultaneously, as they did not expect to reach a sufficient number of children at the same time. Thus, the two programmes will be delivered successively. The programme to be delivered will be determined at random.

In case of further recruitment challenges, outpatient alcohol and drug treatment facilities can be integrated as additional study centres. These facilities have close contact to parents with SUD and, sometimes, offer programmes for CSP, too. By adding this outpatient setting, a comparison of different accesses to CSP can be made.

At last, it is desired to compare the effects of the programme with a naturalistic sample of children from substance-affected families not receiving any intervention. However, this attempt would exceed the study’s resources.

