## Abbreviations

AUDIT: Alcohol Use Disorder Identification Test
CAST: Children of alcoholics screening test
cRCT: Cluster-randomised trial
CSP: Children of substance-abusing parents
DSMB: Data management security board
DUDIT: Drug Use Disorder Identification Test
GCP: Good Clinical Practice
MBSR: Mindfulness-based stress reduction
SAE: Severe adverse event
SUD: Substance use disorder
TAU: Treatment as usual

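### The only adverse-event rule in the article covers unexpected severe events, so a complete account of serious events by programme is not assured

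*Protocol article*

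**What the plan says.** Under Ethical considerations the protocol article sets the rule: "In case of unexpected severe adverse events (SAE) the participating study centres are obliged to document and report these to the research team". A decision on how to proceed then follows case by case. The article states no other duty to record adverse events. Neither *unexpected* nor *severe* is defined, and the list of abbreviations gives "SAE: Severe adverse event".

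On oversight, the same section says: "A neutral data management security board (DSMB) and an external monitoring agency will supervise the adherence of the study to Good Clinical Practice (GCP) standards".

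On the population, the inclusion criteria under Sample require "children currently situated at an inpatient or outpatient psychiatric treatment or psychiatric day care or inpatient youth welfare service".

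Two other passages bear on harm indirectly. Limitations says: "All reasons for rejections and dropouts are to be documented and will be analysed carefully". Data collection has trainers complete "short questionnaires on adherence, group interaction and challenges encountered after each child and parent session".

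**The concern.** Whether an event is expected is a sensible question when deciding how urgently to escalate it. Here it also decides whether there is any duty to write the event down, because the sentence ties documenting and reporting to the same condition. An event that was never recorded cannot be reclassified later.

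The second condition, severity, describes intensity. Seriousness describes consequence. The two can come apart, so an event with a serious consequence but moderate intensity is not clearly covered.

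Both conditions matter in this population. The children are already under psychiatric or youth-welfare care, and worsening of an existing condition is the kind of event that could be called expected. What is at stake is the safety description: how many serious events occurred in each group, and of what kind. The effectiveness analysis is not at stake.

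**Working it through.** The article gives no adverse-event rate, harm endpoint or safety boundary, so there is no figure to reproduce. The check sets the rule beside the rest of the document.

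**Step 1. What the rule covers.** Take an event that is serious by its consequence. It may be expected or not, and severe in intensity or not, which gives 2 × 2 = 4 combinations.

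| Serious event | Severe | Not severe |
|---|---|---|
| Unexpected | covered | not clearly covered |
| Expected | not covered | not covered |

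Read literally, the duty clearly covers one combination of four. If *severe* is only a slip for *serious*, the whole unexpected row is covered, which is two of four. The expected row stays outside on either reading. The gap therefore does not depend on how that word is read.

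**Step 2. Whether the uncovered row matters here.** By the inclusion criteria every child is in psychiatric treatment, psychiatric day care or inpatient youth welfare. Anticipated serious events are plausible in such a group. How frequent they are cannot be said from the article.

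**Step 3. Whether other records close the gap.**

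| Record (section) | What it captures | What it misses |
|---|---|---|
| Dropout reasons (Limitations) | events that lead a child to leave | events in children who stay |
| Trainers' session questionnaires (Data collection) | difficulties in and around sessions | the six months to T2, and the TAU group, which has no sessions |
| Outcome scales at T0, T1 and T2 (Data collection, Table 1) | the level of problems and distress in all three groups | discrete events between measurements |
| Treatment-as-usual items from child and parent (Table 1) | possibly changes in care; the items are not shown | cannot be judged |
| Invitation to call the research group (Ethical considerations) | what families choose to raise | everything else, as it is voluntary |

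Each record captures some harm. None of those that can be judged is a systematic log of serious events covering all groups from T0 to T2.

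**Step 4. What follows for comparison between groups.** If anticipated serious events need not be recorded, a table of serious events by programme may be incomplete by an unknown amount. Even with full recording, only Trampoline-Mind versus Trampoline would be a randomised comparison. Trial design describes control group II (TAU) as a natural group outside the randomisation, so its event counts could be described but not compared on the same footing.

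**The case against.** The strongest defence is that this is a condensed article. Event definitions, forms, the handling of expected events and the board's remit usually stand in the full protocol or a safety manual, neither of which is shown. Their absence here is no finding, and that part of the defence stands. It does not dispose of the point, because the article does more than stay silent: it states a restrictive rule. If the full protocol is broader, the sentence misdescribes it. If not, the gap is real. Either way the sentence should be corrected.

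A second defence is that *severe* is a language slip, which is plausible: no intensity grading is described anywhere. As Step 1 shows, the restriction to unexpected events remains.

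A reader might also infer several stronger things that the document does not support:

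- **That anticipated serious events go unrecorded.** The sentence sets a minimum duty and does not forbid wider recording. The supportable wording is that such events need not be recorded.
- **That marked worsening would never be seen.** The scales are given to all three groups at three time points, and dropout reasons are documented, so part of it would be seen.
- **That the board is prevented from comparing harm.** The board and the monitor "will supervise the adherence of the study to Good Clinical Practice (GCP) standards". No comparison of harm is assigned to the board, so none can be shown to fail.
- **That centre staff who know the programme judge expectedness, so under-recording differs by arm.** Centres document and report, but the article names nobody as judging expectedness. Differential recording is possible but not shown.
- **That the article calls the safety of mindfulness practice untested.** Its remark under Aims and objectives concerns effectiveness in preventing substance-use and related disorders in this group.

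**Conclusion.** The point holds in a limited form. The one adverse-event rule that the article states makes documentation conditional on an event being both unexpected and severe. Serious events that could be anticipated in this population, and serious events of moderate intensity, therefore need not be recorded. A complete description of serious events by programme is not assured.

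The size cannot be given: no event rate is stated, and any assumed rate would be invented. No stated hypothesis or outcome depends on event counts, so this is a minor improvement to safety information and no threat to the main result.

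The conclusion assumes that centres apply the sentence as written and that no broader instruction exists in documents not shown. If one does exist, only the article's wording needs correction.

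**What to change.** Replace the reporting sentence with: *All serious adverse events from T0 to T2, expected or not and related or not, are documented in all three groups and reported to the research team.* Correct the abbreviation to serious adverse event, in the text and in the list.

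Have the research team classify expectedness and relatedness after the report has arrived, so that neither decides whether an event is written down. Tabulate serious events by group in the final report. Limit the randomised comparison to Trampoline-Mind versus Trampoline, and show the TAU group descriptively.

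If the full protocol already requires this, bring the article's sentence into line with it; nothing more is needed.

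The cost is one amended sentence, a short event form and slightly more paperwork for centres. Clinical management, the sample size and the primary analysis do not change.

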## Discussion

### Summary

Despite the existing evidence-based “Trampoline”-programme, there is a substantial need for the improvement of care targeting CSP. Even though “Trampoline” has been proven to be effective, the significance of effect were small, and emotion regulation skills can be enhanced further. These skills are key when it comes to coping with stress.

One promising idea for improving the programme is the integration of elements of mindfulness-based trainings, as these may be able to enhance CSP’s socioemotional resilience and self-regulatory processes [31–33], including emotion regulation [34].

Hence, a mindfulness-augmented version of the original “Trampoline”-programme (“Trampoline-Mind”) for CSP aged 8–12 years was developed and tested in a multicentre cRCT with three points of measurement (pre, post and follow-up) while comparing it to the original “Trampoline”-programme and TAU. It is expected that participants in the “Trampoline-Mind” will benefit from the integration mindfulness components into the “Trampoline” programme by demonstrating enhanced stress regulation skills compared to the participants from the original “Trampoline” and the TAU condition. This study will also enlarge the evidence on mindfulness-based interventions for children and adolescents in clinical and youth welfare settings.

### Implications

The intervention and its study design have several strengths: first, “Trampoline-Mind” is based on an evidence-based intervention tailored to the needs of CSP. It both considers theoretical foundations and practical experiences from the work with CSP. Second, the intervention can be delivered easily by professionals due to the self-explanatory trainer’s manual. “Trampoline-Mind” thus may be regarded as a pragmatic programme that can be used in clinical and youth welfare settings as well. Third, because of the strict separation between trainers and programme evaluators, bias is reduced. A further reduction of bias is achieved by gathering not only data form children’s self-reports but also from their parents’ point of view. Fourth, by conducting a 6-month follow-up, sleeper effects can be detected, and the stability of effects uncovered in the post-measurement can be tested. Fifth, the effects of “Trampoline-Mind” are compared to both the original “Trampoline”-programme and TAU. Therefore, specific effects of mindfulness-based elements and addiction-specific contents can be identified.

Study results will be disseminated within the scientific community via journal publications and presentations.

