### Aims and objectives of the study

The aim of our ongoing study is to assess the effectiveness of a mindfulness-augmented version of the original “Trampoline”-programme (“Trampoline-Mind”) for children aged 8–12 years, have at least one substance-abusing parent and are suffering from emotional and/or behavioural problems. The effectiveness of the intervention will be tested in a multicentre cluster-randomised controlled trial with three points of measurement (pre, post and follow-up) while comparing it to the original “Trampoline”-programme and treatment-as-usual (TAU). It is hypothesised that “Trampoline-Mind” is feasible and effective for CSP and has had a positive impact on relevant predictors of SUD and other mental disorders. In detail, a mindfulness-augmented version of “Trampoline” is expected to improve children’s application of stress coping strategies in favour of problem-focused stress coping and constructive-palliative emotion regulation over avoidant stress coping and destructive-anger-related emotion regulation compared to the established “Trampoline”-programme. This suggests that CSP can benefit from integrating mindfulness components in the existing programme. As a secondary hypotheses, it is expected that “Trampoline-Mind” reduces distress due to parental substance use as well as internalising and externalising problem behaviours more effectively than the original “Trampoline” programme.

Moreover, by including mindfulness elements and using reliable and objective measures in a rigorous research design, this study allows the evidence on mindfulness-based interventions to be enlarged. Mindfulness training has an established evidence base, but only for adults [34]. Nevertheless, recent research has also supported the feasibility and efficacy of mindfulness-based techniques for children and adolescents [32, 39]. However, the current evidence is largely restricted to non-clinical settings, such as school settings [34], and it remains untested whether mindfulness-based interventions are effective in the prevention of SUD and related disorders among a highly vulnerable group such as CSP. Therefore, the study presented here will make use of a cluster-randomised-controlled trial longitudinal study design to establish profound evidence on the efficacy of the mindfulness-based “Trampoline-Mind” programme in a clinical and youth welfare setting, targeting the highly vulnerable group of CSP.

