### Trial design

The 9-session group programme “Trampoline-Mind” for children from substance-affected families is currently tested with regard to its effectiveness in a multicentre cluster-randomised trial (cRCT). The study presented here will compare the new “Trampoline-Mind” version (intervention group) to a) the original “Trampoline”-programme (control group I) with the same duration as “Trampoline-Mind” and b) a TAU-group (control group II). Both the intervention group and the control group I are delivered in the project facilities mentioned above. The programme to be delivered will be determined by randomisation which will be performed computer-based by the research team at Catholic University of Applied Sciences North Rhine-Westphalia. Control group II is a natural group that is not a part of the randomisation. Data from all three groups are gathered at three points: prior to intervention (T0), immediately after the intervention (T1) and six months after (T2). Last data collections for T2 are scheduled for January 2021.

The programme is designed for 8 to 12-year olds; exceptions can occasionally be made for 7- and 13-year-old children, depending on their developmental status. At baseline (T0), 420 children from 84 clusters are intended to enter the programme. Each cluster consists of an average size of five children.

The procedure of this study is presented in Fig. 1.

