### Interventions

The original “Trampoline”-programme, which control condition I receives, is a standardised, manualised group intervention that consists of nine modules for children and one module for parents (one part before the first child module and the other after the last child module). The envisaged group size is approximately five children, with every group moderated by two trained trainers. One module lasts 120 min, including a break matching the duration of the mindfulness-augmented modules. The original “Trampoline” modules will employ the following standard elements:Module 1 – getting to know each otherModule 2 – self-worth: how I feel about myselfModule 3 – alcohol and/or drug problems in my familyModule 4 – knowledge: what I need to know about drugs and addictionModule 5 – handling difficult emotionsModule 6 – self-efficacy: what I can do to solve problemsModule 7 – learning new patterns of behaviour in my familyModule 8 – what I can do to find help and supportModule 9 – a positive good-bye

The original “Trampoline”-programme thus contains elements of psychoeducation, emotion regulation skills, strengthening of self-efficacy and self-worth, stress management and problem-solving strategies. All sessions follow the same structure and include recurring small rituals, as predictability is of major importance to children from substance-involved families.

The mindfulness-augmented version, “Trampoline-Mind”, which is delivered to the intervention group, maintains the structure, format and content of “Trampoline”, but adds 30 min of mindfulness-related exercises to each module. Core mindfulness dimensions will be included, such as present-moment awareness, body awareness and mindful movement, relaxation, mindfulness in dealing with emotions and thoughts, attention and non-judgmental acceptance, self-acceptance and self-compassion and kindness towards self and others. The development of the mindfulness exercises is based on a rigorous review of available evidence of mindfulness-based interventions for young people and according to the developmental needs and characteristics of children aged 8–12 years (e.g. cognitive abilities such as information processing, reasoning, language development, memory, attention span, knowledge of concepts and environmental requirements).

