The parent module is the same for both the groups under study. It contains information and sensitisation on growing up in a substance-affected family, exercises on positive parenting, feedback on the course of the children’s groups and motivation for use of further help and support.

Both “Trampoline-Mind” and the original “Trampoline”-programme are delivered by trained trainers with a professional background in social work, psychology or similar.

No “Trampoline”-intervention is delivered to participants in control intervention II; this group will receive TAU only.

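### The TAU group is not randomised, so the trial cannot identify a specific effect of the addiction-specific content as the article claims

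*Protocol article*

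**What the plan says.** **Allocation.** Under Trial design, the article says of the TAU arm: "Control group II is a natural group that is not a part of the randomisation". Ethical considerations gives the routes in: "Participants from control condition II have volunteered to participate in this group or are assigned to it for practical reasons". Under Interventions, no Trampoline programme is delivered to it: "this group will receive TAU only".

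**Use of the TAU arm.** Aims and objectives of the study states: "The effectiveness of the intervention will be tested in a multicentre cluster-randomised controlled trial with three points of measurement". The same sentence names original Trampoline and TAU together as the comparators. The Discussion's Summary repeats this and expects better stress regulation with Trampoline-Mind than in either group.

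**Conclusion drawn.** Implications gives the comparison with both groups as the fifth strength of the design and ends: "Therefore, specific effects of mindfulness-based elements and addiction-specific contents can be identified". No section describes the TAU comparison as observational. Limitations discusses selection into the sample, but not the non-random formation of the TAU group.

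**The concern.** The quoted conclusion has two halves, and they rest on different contrasts. The mindfulness half rests on Trampoline-Mind versus original Trampoline, which is randomised. The addiction-specific half can rest only on a contrast with TAU, which is not. The article treats both alike and places both under the cluster-randomised trial.

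At stake is how a TAU result will be read. A difference from TAU, reported as part of a cluster-randomised effectiveness test, would be taken as the causal effect of the addiction-specific modules. It could instead reflect who ended up in TAU, or simply nine sessions of group contact. Selection could equally hide a real effect.

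**Working it through.** **Step 1: which contrast carries which claim.** The arms, as described under Interventions and Trial design:

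| Arm | Addiction-specific content | Mindfulness | Trampoline group sessions | Randomised |
|---|---|---|---|---|
| Trampoline-Mind | yes | yes | nine | yes |
| Original Trampoline | yes | no | nine | yes |
| TAU | no | no | none | no |

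The mindfulness version keeps the content of the original programme, so the addiction-specific column does not vary between the randomised arms. It varies only against TAU. In that comparison, randomisation status and group attention change at the same time. Even without selection bias, a TAU contrast would estimate the effect of the whole group programme, not of its addiction-specific part.

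**Step 2: the plan's own figure.** The only calculated figure is 420 children from 84 clusters (420/84 = 5 per cluster), under Statistical analyses. The article gives no numeric effect size, intracluster correlation (ICC) or allocation ratio, and does not say whether the 420 includes TAU. The figure can therefore be neither reproduced nor refuted, and this point does not depend on it.

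**Step 3: how much selection would matter (illustration).**

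Inputs from the article: two-sided alpha 0.05; maximum dropout 30%; mean cluster size m = 5.

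Assumptions: three equal groups within the 420, so n = 420/3 × 0.7 = 98 completers per group; ICC 0 or 0.05, with the design effect applied to both groups; true effect zero; a difference of b SD between TAU and the comparator that remains after any adjustment.

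Formulas, with the outcome in SD units:

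- Design effect: DE = 1 + (m − 1) × ICC, which is 1.0 at ICC 0 and 1 + 4 × 0.05 = 1.2 at ICC 0.05.
- Standard error: SE = √(2 × DE/n), which is √(2/98) = 0.1429 and √(2.4/98) = 0.1565.
- Rejection probability: 1 − Φ(1.96 − b/SE) + Φ(−1.96 − b/SE).

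For b = 0.2 and ICC 0, b/SE = 1.40, so the probability is 1 − Φ(0.56) + Φ(−3.36) = 0.288. For ICC 0.05, b/SE = 1.278, so it is 1 − Φ(0.682) + Φ(−3.238) = 0.248.

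| Residual difference b | ICC 0 | ICC 0.05 |
|---|---|---|
| 0 | 5% | 5% |
| 0.1 SD | 10.8% | 9.8% |
| 0.2 SD | 28.8% | 24.8% |
| 0.3 SD | 55.6% | 48.3% |

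The sample size is said to target small effects. If small means about 0.2 SD (the conventional value; the article gives none), a residual selection difference of that size would by itself mimic the effect sought.

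**The case against.** Much can be said for the plan, and some of it stands.

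- **The hypotheses do not rest on TAU.** The Abstract and the Aims state the primary and secondary hypotheses against original Trampoline only. This stands. A reader might infer that the trial's main result is compromised; it is not.
- **Nothing is concealed.** Trial design says openly that TAU is not randomised. This also stands. The fault is that the Aims, Summary and Implications do not carry that fact into what they claim.
- **Adjustment may be planned in an analysis plan that is not shown.** A reader might infer that an unadjusted TAU comparison is intended, but the article does not say so, and the absence of covariates from it is no fault. Adjustment would, however, deal only with measured factors. It would neither support an unqualified claim of identification nor separate content from group attention.
- **The direction and cause of selection are unknown.** It is tempting to argue that parental denial and shame sort families into TAU, because Limitations says that "many parents with SUD will not let their children participate in the programme because of denial or feelings of shame and guilt". That passage concerns refusal of the programme and a resulting selection effect in the sample. It does not say that refusers enter TAU. TAU members also need written consent, so such families may be missing from every group. Nor is the group purely self-selected, since practical assignment is a second route. The point needs only that neither route is random.
- **The mindfulness half might seem equally weak.** The original programme fills time with a break ("One module lasts 120 min, including a break matching the duration of the mindfulness-augmented modules"), while Trampoline-Mind adds 9 × 30 = 270 min of exercises. A reader might infer that mindfulness is confounded with extra structured activity. The documents do not carry that far: the contrast is randomised and matched on duration, and neither the length nor the content of the break is given. Preferring an active control to a break is a design preference.
- **The error rates are assumed.** This is correct. The article gives no TAU group size, selection difference or ICC. The figures show scale only.

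**Conclusion.** The point holds for the addiction-specific half of the sentence in Implications, and for the wording in the Aims and Summary that puts the TAU comparison inside the cluster-randomised effectiveness test. The article claims a property that the design lacks. This follows from the text alone: TAU is not randomised, both randomised arms share the content in question, and TAU has no matched group contact.

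The size is illustrative. With 98 per group and a residual difference of 0.2 SD, the nominal 5% error becomes about 25 to 29% (ICC 0.05 to 0). The range runs from about 10 to 11% at 0.1 SD to 48 to 56% at 0.3 SD. Group size, selection difference and ICC are all assumptions. The finding does not extend to the randomised contrast with original Trampoline.

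**What to change.** 1. In the Aims, Summary and Implications, state that Trampoline-Mind versus original Trampoline is the only randomised, confirmatory contrast.
2. Report every TAU contrast as non-randomised and exploratory. Adjust for the T0 value of the outcome and for other baseline information available in all groups: age, setting, AUDIT/DUDIT, CAST-6 and the parent-version SDQ (the child version is given only from age 11). Add a T0 balance table. Describe how children came into TAU, but do not use that route as a covariate, because it is defined only within the TAU group.
3. Delete the addiction-specific part of the Implications sentence, or restate it as an exploratory, non-causal comparison of a group programme with usual care.

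The cost is wording and one adjusted analysis of measures already planned. The sponsor gives up a causal claim against TAU.
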